## Abstract

**Background:**

A key decision in the treatment of atrial fibrillation is choosing between a rhythm control strategy or a rate control strategy as the main strategy. When choosing rate control, the optimal heart rate target is uncertain. The Danish Atrial Fibrillation trial is a randomized, multicenter, two-group, superiority trial comparing strict rate control versus lenient rate control in patients with either persistent or permanent atrial fibrillation at inclusion. To prevent bias arising from selective reporting and data-driven analyses, we developed a predefined description of the statistical analysis.

**Methods:**

The primary outcome of this trial is the physical component score of the SF-36 questionnaire. A total of 350 participants will be enrolled based on a minimal important difference of 3 points on the physical component score of the SF-36 questionnaire, a standard deviation of 10 points, a statistical power of 80% (beta of 20%), and an acceptable risk of type I error of 5%. All secondary, exploratory, and echocardiographic outcomes will be hypothesis-generating. The analyses of all outcomes will be based on the intention-to-treat principle. We will analyze continuous outcomes using linear regression adjusting for “site,” type of atrial fibrillation at inclusion (persistent/ permanent), left ventricular ejection fraction (≥ 40% or < 40%), and the baseline value of the outcome (all as fixed effects). We define our threshold for statistical significance as a *p*-value of 0.05 and assessments of clinical significance will be based on the anticipated intervention effects defined in the sample size and power estimations. Thresholds for both statistical and clinical significance will be assessed according to the 5-step procedure proposed by Jakobsen and colleagues.

**Discussion:**

This statistical analysis plan will be published prior to enrolment completion and before any data are available and is sought to increase the validity of the DANish Atrial Fibrillation trial.

**Trial registration:**

Clinicaltrials.gov NCT04542785. Registered on Sept 09, 2020.

**Supplementary Information:**

The online version contains supplementary material available at 10.1186/s13063-023-07247-7.

## Background

Atrial fibrillation is the most common arrhythmia of the heart with a prevalence of approximately 2 to 4% in the western world [1]. A key decision in the treatment of atrial fibrillation is choosing between a rhythm control strategy and a rate control strategy as the main treatment strategy. When choosing rate control, the optimal heart rate target is uncertain [1].

Current guidelines consider lenient rate control acceptable as the initial rate-controlling strategy [1]. This recommendation is primarily based on the results of the RACE II trial [2]. The Danish Atrial Fibrillation (DanAF) trial is a randomized, two-group, multicenter, superiority trial that plans to investigate which heart rate target is superior regarding quality of life in patients with atrial fibrillation [3].

The present publication will summarize the statistical analysis plan to ensure that the trial is analyzed according to a prespecified plan as recommended by The International Conference on Harmonization of Good Clinical Practice, among others, to prevent bias arising from selective reporting and data-driven analyses [4, 5]. The trial is registered with Clinicaltrials.gov: NCT04542785.

## Methods

The design of this trial has been described in detail in our protocol for this trial [3]. The flow of the recruitment, exclusion, and randomization process is displayed in a Consolidated Standards of Reporting Trials flow diagram (CONSORT) (see Fig. 1) [6].

**Fig. 1 Fig1:**
[figure not shown]
CONSORT flow diagram

**Inclusion criteria**
Participants with either persistent (defined as atrial fibrillation lasting for more than 7 days) or permanent (rate control is considered the only treatment option) atrial fibrillation confirmed by 12-lead electrocardiogram (ECG) at inclusion. Participants with postoperative atrial fibrillation who meet the listed inclusion criteria and none of the exclusion criteria will be eligible as well.Rate control must be accepted as the primary management strategy.Informed consent.Adult (18 years or older).

**Exclusion criteria**
No informed consentInitial heart rate below 80 bpm at rest (assessed by 12-lead ECG before randomization)Oral anticoagulant therapy of non-vitamin K oral anticoagulants (NOACs) of less than 3-week duration or warfarin with international normalized ratio (INR) levels within therapeutic range or less than 4 weeksIf the treating physician deems that the participant is not suitable to be randomized into both groups based on an individual assessment. This decision will be made before randomization by the treating physician. This can, for example, include participants depending on a high ventricular rate to maintain a sufficient cardiac output, such as patients with heart failure, a hemodynamically significant valve dysfunction, or severely dehydrated participantsParticipants who are hemodynamically unstable and therefore require immediate electrical cardioversion

### Randomization

This trial uses centralized randomization at Open Patient data Explorative Network (OPEN), where varying block sizes unknown to the investigators will be used. Randomization is stratified for (1) site of inclusion, (2) persistent/permanent atrial fibrillation (6 months before inclusion), and (3) left ventricular ejection fraction (LVEF) (≥ 40% or < 40%). Participants are be randomly allocated to the lenient versus the strict rate control strategy arm in an 1:1 ratio [3].

### Participant withdrawal

Participants can withdraw his or her consent at any time point for any reason. The participants will be asked if he or she will still participate in the follow-up assessment(s). As treatment follows standard treatment for atrial fibrillation and any treatment clinically indicated is accepted, there are no other reasons that will result in participants being withdrawn [3].

### Trial interventions

It is up to the clinician to treat the patient with the guideline-appropriate heart rate-reducing agents [1]. This is further explained in the protocol of this trial, and the European Society of Cardiology guidelines, who list the suggested agents and doses to achieve rate control [1, 3].

#### Lenient rate control

For lenient rate control, the treatment provider will target the highest tolerable resting heart rate < 110 bpm assessed on a 12-lead resting ECG measured over 1 min after 5 min of rest. If the heart rate is below 90 beats per minute, the responsible physician is encouraged to reduce rate-controlling drugs.

#### Strict rate control

For strict rate control, the treatment provider will target a mean resting heart rate of 70 bpm, but < 80 bpm is acceptable. The heart will be assessed on a 12-lead resting ECG measured over 1 min after 5 min of rest.

A more detailed description of the interventions can be found in the protocol, which previously has been published [3].

### Outcomes

We want to assess all relevant outcomes. To limit problems with multiplicity, we define outcome hierarchies. The outcomes are defined as primary, secondary, exploratory, and echocardiographic outcomes. The sample size (see “Sample size” section) is based on the primary outcome and our primary conclusions will be based on the results of the primary outcome. The results from secondary, exploratory, and echocardiographic outcomes will be considered hypothesis-generating only.

#### Primary outcome

Quality of life using the SF-36 questionnaire (physical component score)

#### Secondary outcomes

Hospital-free days (HFDs), analyzed as count data. We define HFDs as all days alive that are spent outside an acute-care hospital, long-term acute-care hospital (LTACH), or in an emergency department (ED), including days spent wholly or in part under “observation” status. All other days, including days spent in a long- or short-stay nursing facility, inpatient hospice facility, or rehabilitation facility count as hospital-free, as would all days at home, including those with home-based medical services [7]Symptoms due to atrial fibrillation assessed using the Atrial Fibrillation Effect on Quality-of-Life questionnaireQuality of life using the SF-36 questionnaire (mental component score)Serious adverse events, defined according to The International Conference on Harmonization as any untoward medical occurrence that resulted in death, was life-threatening, required hospitalization or prolongation of existing hospitalization, and resulted in persistent or significant disability or jeopardized the patient [4]

#### Exploratory outcomes

All-cause mortalityComposite of all-cause mortality, stroke, myocardial infarction, and cardiac arrestStrokeHospitalization for worsening of heart failureNumber of hospital admissions, analyzed as count dataSix-minute walking distanceHealthcare costs (will be further defined and reported in separate publications)Various biomarkers (N-terminal pro-brain natriuretic peptide (nt-proBNP), high-sensitivity C reactive protein (hsCRP), high-sensitivity troponin I (hsTnI), growth differentiation factor-15 (GDF-15), interleukin 6 (IL6), cystatin-C, YKL40, soluble urokinase plasminogen activator receptor (suPAR), and fibulin-1Switch to rhythm control strategy (such as rhythm control medication, direct current-conversion or pharmacological cardioversion, pulmonary vein isolation, or arrhythmia surgery)Implantation of a pacemaker or cardioverter-defibrillator with or without atrioventricular nodal ablation

#### Echocardiographic outcomes

A detailed description of the echocardiographic analysis principles can be found in supplemental file 1. Additionally, we will develop and publish a separate echocardiographic statistical analysis plan.

The following outcomes will be assessed in a core-echo lab:Left atrial size (left atrial volume index)Left ventricular sizeCardiac index (cardiac output/body surface area)Left ventricular ejection fractionTricuspid annular plane systolic excursion (TAPSE)Midwall fractional shorteningGlobal longitudinal strainCircumferential end-systolic stressDiastolic dysfunction estimated by the relationship between left ventricular filling and the interval between two successive R waves on ECG (R-R interval) for the individual patientPulmonary pressure

#### Subgroup analysis

The subgroup analyses will be performed for primary and secondary outcomes and all subgroup analyses will be regarded as hypothesis-generating only. These analyses will be tested for interactions using test of interaction (interaction between the treatment variable and the subgroup indicator) in STATA 17 [8].

We will compare the following subgroups between the intervention arms:Patients with heart failure (including subtypes) compared to patients without heart failure [9]◦ Heart failure with reduced ejection fraction LVEF ≤ 40% or mildly reduced ejection fraction LVEF 41–49% (HFrEF and HFmrEF)◦ Heart failure with preserved ejection fraction LVEF ≥ 50% (HFpEF)Patients compared by their New York Heart Association (NYHA) class◦ NYHA class: I◦ NYHA class: II◦ NYHA class: III and IVPatients who are men compared to patients who are womenPatients compared based on their different durations of atrial fibrillation at randomization. The starting point of the duration of atrial fibrillation will be defined by when the patient was clinically diagnosed with persistent atrial fibrillation◦ Less than 1 year◦ 1 to 2 years◦ More than 2 yearsPatients who are 75 years of age or older compared to patients below 75 years of agePatients according to the modified European Heart Rhythm Association (mEHRA) symptoms score [10]◦ mEHRA score: 1, 2a, and 2b◦ mEHRA score: 3 and 4Patients having persistent atrial fibrillation compared to patients having permanent atrial fibrillation. Persistent atrial fibrillation defined as atrial fibrillation for more than 7 days and permanent atrial fibrillation defined as where only rate control is considered going forwardPatients achieving the target heart rate compared to patients not achieving the target heart rate

### Sample size

We estimated the required sample to be a total of 350 participants based on a minimal important difference of 3 points on the physical component score of the SF-36 questionnaire, a standard deviation (SD) of 10 points, power of 80%, and an acceptable risk of type I error of 5% [3].

#### Power estimations of secondary and exploratory outcomes

All power estimations below are based on the sample size estimation of 350 participants. The remaining power estimations can be found in supplemental file 2.

#### Hospital-free days

Using a minimal important difference of 3 days, a SD of 9 days, a risk of type I error of 5%, and accounting for the fact that the data is expected not to be normally distributed (adding 15% to the required sample size) [11], we will be able to reject the null hypothesis that the population means of the experimental and control groups are equal with probability (power) of 82.1% [12].

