#### Serious adverse events

Using a proportion of participants with one or more serious adverse events in the control group of 20%, a relative risk reduction of 30%, and a risk of type I error of 5%, we will be able to reject the null hypothesis with probability (power) of 32%.

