##### Analysis of count data

Count data will be presented as medians and interquartile ranges. We will analyze count data using van Elteren’s test stratifying for “site” and report Hodges Lehman median differences and confidence intervals [12, 23, 24].

An example of a count outcome is collected from the following outcome: “Number of hospital admissions.”

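### The 82.1% power quoted for hospital-free days belongs to a comparison of means with SD 9, not to the van Elteren test planned for this outcome

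*SAP article*

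**What the plan says.** The section on power for secondary and exploratory outcomes fixes the sample: "All power estimations below are based on the sample size estimation of 350 participants". Randomization is to the "lenient versus the strict rate control strategy arm in an 1:1 ratio", so 175 per arm. The Hospital-free days paragraph then sets the inputs, "Using a minimal important difference of 3 days, a SD of 9 days, a risk of type I error of 5"%, makes an adjustment, "accounting for the fact that the data is expected not to be normally distributed (adding 15% to the required sample size"), and concludes that the trial can "reject the null hypothesis that the population means of the experimental and control groups are equal with probability (power) of 82.1"%.

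The outcome and its analysis are fixed elsewhere. Under Secondary outcomes: "We define HFDs as all days alive that are spent outside an acute-care hospital" and certain other acute settings, to be analysed as count data. Under Analysis of count data the test is van Elteren's, stratified by site, and the authors will "report Hodges Lehman median differences and confidence intervals". The primary timepoint is 12 months. General analytic principles says that clinical significance will be judged against the effects anticipated in the sample size and power estimations, which for this outcome is 3 days.

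**The concern.** The power statement concerns equality of population means, whereas the planned test compares ranks and the planned estimate is a Hodges-Lehmann difference. For a roughly symmetric outcome this would hardly matter. This one is capped at about 365 days, many participants are likely to sit at the cap, and a death removes every remaining day of the year. In such a distribution the SD is driven by a few deaths, and the rank test is driven largely by how many participants lose any day at all. A 3-day difference in means with SD 9 describes neither.

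Hospital-free days is the first secondary outcome listed. A null result would be read against a stated power of 82%, and a positive one against a 3-day threshold that the planned estimate may be unable to show.

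**Working it through.** **1. Reproducing the stated figure.** Inputs from the SAP: difference 3, SD 9, 5% type I error (two-sided assumed), 350 participants, 1:1, 15% allowance.

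- Effective size: 350/1.15 = 304, about 152.2 per arm.
- Standard error: 9 × √(2/152.2) = 1.03.
- Power: Φ(3/1.03 − 1.96) ≈ 82.8%; the t-test version gives 82.6%.
- Taking 15% off instead (175 × 0.85 = 148.75 per arm) gives 82.0%.
- With no allowance, 175 per arm gives 87.7%.

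The stated 82.1% lies within this range of adjusted figures.

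**2. Is SD 9 compatible with counting only days alive?** Suppose a proportion p die, at times uniform over 365 days, and nothing else varies. The SD of days lost is √(p × 365²/3 − (p × 182.5)²).

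- Setting this to 9 gives p = 0.18%, or 0.64 deaths in 350.
- The SAP gives no death rate, so the rates below are assumptions. Power is for means at 152 per arm.

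| Assumed 12-month mortality | SD from deaths alone | Power for means |
|---|---|---|
| 1% | 21.0 | 24% |
| 2% | 29.6 | 14% |

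**3. Power of the planned test.** For a pure normal shift of 3 with SD 9, simulated van Elteren power (175 per arm, five strata for the five sites in Table 1, 3000 runs) is 84.7%. The 15% allowance is therefore adequate in that case.

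The outcome was then simulated as 365 days minus hospital days, with most participants losing none and a mean difference near 3 days. Proportions and stay lengths are assumptions.

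| Source of the 3-day difference | Rank-test power |
|---|---|
| Length of stay only, equal proportions | about 8–10%; up to 31% with 50% hospitalised |
| 20% vs 14% hospitalised | 30–46% |
| 30% vs 21% | 63–68% |
| 40% vs 28% | 80–86% |
| 50% vs 35% | 92–93% |

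Within a row, power also depends on stay length. With equal stays in both arms, 40% vs 28% needs a mean stay of 3/(0.40 − 0.28) = 25 days to give a 3-day difference, and power is then about 63%. If the whole difference comes from deaths (3% vs 1.4%), power is about 6%. If it comes only from a very large drop in the proportion hospitalised (0.35 to 0.35 − 3/12 = 0.10, mean stay 12 days), power is about 100%.

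**4. The planned estimate.** The Hodges-Lehmann estimate is the median of all between-arm pairwise differences. At 20% vs 14%, 0.80 × 0.86 = 69% of pairs are exactly zero, so the median is 0. At 40% vs 28%, at most 40% of pairs can favour one arm and at most 28% the other. Neither reaches half, so the median is again 0. At 50% vs 35% the same bound leaves it at about 0. The means differ by 3 days in every case.

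**The case against.** The figure is not miscalculated, and the authors foresaw non-normality: their allowance is a recognised approximation to rank-test efficiency, and under a location shift 82.1% is slightly conservative. The sources cited for it are not at hand. All of that stands. It does not help here, because a ceiling-bound, heavily tied outcome does not move by a location shift.

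Deaths inflate the SD but barely disturb ranks. With 2% deaths in each arm, rank-test power was about 39% at 20% vs 14% hospitalised and 83% at 40% vs 28%, close to the values without deaths. This also stands: the SD argument undermines the stated mean-based figure but does not show that the planned test is weak.

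A reader might infer that true power is about half of 82% or less. The SAP does not support that. The 20% vs 14% comes from its serious adverse event paragraph ("Using a proportion of participants with one or more serious adverse events in the control group of 20%, a relative risk reduction of 30"%), which is a different outcome. Days in an emergency department or under observation also count against hospital-free days, so the proportion losing a day may be higher, and at 40–50% hospitalised the power can reach or exceed 82%.

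A reader might also say that any single death in 350 pushes the SD above 9. With no other variation, one death gives an SD of days lost/√350. This exceeds 9 only if more than about 168 days are lost, that is, for a death before about day 197; a mid-year death gives 9.76.

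Nor do the Limitations wrongly leave this outcome out. They give mortality and serious adverse events as examples, not as a complete list.

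**Conclusion.** The point holds as a mismatch between the stated power and the planned analysis, not as an arithmetic error. The 82.1% is a sound calculation for means with SD 9, but that SD implies fewer than one death in 350 under uniform death times. For the van Elteren test, a 3-day mean difference does not determine power. Under the assumed proportions and stay lengths it ranges from about 8% to 93%, with still wider extremes possible, and it can fall on either side of 82.1%. The direction is therefore open, but power well below 80% is a real possibility if few participants are hospitalised. Separately, the Hodges-Lehmann estimate is about 0 in these scenarios, so it cannot be set against the 3-day threshold that General analytic principles takes from the power paragraph.

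Mortality, proportion hospitalised and length of stay are all assumptions, since the SAP gives none of them. The outcome is secondary and declared hypothesis-generating, so the sample size and the primary conclusion are unaffected. The correction is worth making but not critical.

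**What to change.** 1. Replace 82.1% with simulated power for van Elteren's test stratified by site, under stated assumptions on mortality, proportion with any hospital day and length of stay. Show it as a range, for example 20–50% hospitalised and 0–2% deaths, counting days after death as not hospital-free.
2. Add a sentence that power may be well below 80% if few participants are hospitalised.
3. Beside the rank test, report the difference in mean hospital-free days with a bootstrap confidence interval, so that the 3-day difference can be assessed.

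The cost is a less favourable stated figure, one short simulation and one extra summary in the results. Enrolment, data collection and the primary analysis stay as they are.

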#### The Atrial Fibrillation Effect on Quality-of-Life

Using a minimal important difference of 7 points, a SD of 21 points, and a risk of type I error of 5%, we will be able to reject the null hypothesis that the population means of the experimental and control groups are equal with probability (power) of 87.5% [13, 14].

#### Quality of life using the SF-36 questionnaire (mental component score)

Using a minimal important difference of 4, a SD of 10, and a risk of type I error of 5%, we will be able to reject the null hypothesis that the population means of the experimental and control groups are equal with probability (power) of 96% [15–17].

#### Serious adverse events

Using a proportion of participants with one or more serious adverse events in the control group of 20%, a relative risk reduction of 30%, and a risk of type I error of 5%, we will be able to reject the null hypothesis with probability (power) of 32%.

### Timeframe of analyses and investigations

Investigations of this trial will take place at the baseline visit, followed by a 1-month, 2-month, 6-month, and 12/24/36-month visits. A margin of 2 weeks + / − of each visit will be allowed. Further visits might be needed to achieve the desired rate. A more detailed description of the timeframe of investigations can be found in Table 2 of the protocol [3].

The primary analyses of all outcomes of this trial will be performed after all participants have completed a 12-month follow-up (after randomization). The 12-month follow-up will be regarded as our primary analysis timepoint, and the 24-month and 36-month analyses will be considered hypothesis-generating only to limit multiplicity.

Furthermore, an independent data safety monitoring committee (IDSMC) will conduct an interim analysis after 33% of the sample size population has completed 12-month follow-up, to monitor whether the trial still holds scientific merit. The IDSMC will then decide if a new interim analysis should be performed.

A more detailed description of the IDSMC and its interim analyses can be found in the protocol and the supplemental file 6 of the protocol [3].

